**Methods:**

This pragmatic cluster randomized controlled trial will be conducted between December 2019 and June 2021. We will randomize eight operational districts (clusters) in seven provinces (Kampong Cham, Kampong Thom, Prey Veng, Thbong Khmum, Kampong Chhnang, Kandal, and Kampong Speu) to either the control group (PCF) or the intervention groups (ACF using a seed-and-recruit model, ACF targeting household and neighborhood contacts, and ACF targeting persons aged ≥ 55 years using mobile screening units). The primary endpoints will be TB case notification rates, additionality, and cumulative yield of TB cases. The secondary endpoints include treatment outcomes, the number needed to screen to find one TB case, and cost-effectiveness outcome measures. We will analyze the primary and secondary endpoints by intention to treat. We will compare cluster and individual-level characteristics using Student’s *t* test and hierarchical or mixed-effect models to estimate the ratio of these means. The incremental cost-effectiveness ratio per disability-adjusted life year averted will also be considered as a benchmark to determine whether the interventions are cost-effective.

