### Interventions

#### Explanation for the choice of comparators

The PCF strategy is a default setup in the national health system. PCF is a patient-initiated pathway that relies on the self-presentation of presumptive TB cases to the health centers to be diagnosed with TB. Upon screening by health center staff, sputum samples from presumptive TB cases belonging to the KAPs will be collected for examination by GeneXpert or direct smear microscopy if the GeneXpert system is not available. CXR will be performed at the referral hospital if the sputum examination result is negative. TB diagnoses will be made by clinicians based on clinical, radiological, and microbiological evidence. For presumptive TB individuals who present with cough for less than 2 weeks, CXR will be performed at the referral hospital, and sputum samples will be collected for GeneXpert testing if radiological abnormalities are detected [23]. For presumptive TB cases who do not belong to KAPs, smear examination will be performed if presenting with a cough lasting for 2 weeks or more. Those presenting to the health centers with cough for less than 2 weeks will be referred to the referral hospital for CXR, and cases with any radiological abnormalities will undergo smear examination [23]. Newly diagnosed people with TB will be treated and managed according to the national TB guidelines. We will follow-up all people with TB diagnosed during the study period for 6 months from the treatment initiation.

This is a patient-initiated pathway to TB diagnosis involving: a person with active TB experiencing symptoms that he or she recognizes as serious; a person having access to and seeking care, and presenting spontaneously at an appropriate health facility; a health worker correctly assessing that the person fulfills the criteria for presumptive TB; and the successful use of a diagnostic algorithm with sufficient sensitivity and specificity to diagnose TB.

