### Data collection and management

#### Plans for assessment and collection of outcomes

For the primary endpoints, we will collect case notification data from the intervention implementers (CATA, KHANA, CENAT), the provincial health department, and health centers (Table 2). For the secondary endpoints, data on treatment outcomes will be collected from the health centers. To assess the number needed to screen, we will collect screening data and the number of TB cases diagnosed from the intervention implementers, the provincial health department, and health centers. Data on costs—direct and indirect medical costs [29, 30], intervention, diagnostics, and medications—will be collected from the intervention implementers and the baseline and follow-up surveys (Table 2). In the survey, we will document the baseline characteristics of new diagnoses found in all arms using a questionnaire. Information on age, gender, education level, occupation, number of family members and housing, smoking, alcohol use, drug use, TB history, and the presence of other comorbidities will be collected. We will adapt and contextualize the knowledge, attitude, and practice survey instrument tools developed by the WHO to collect information on TB knowledge, attitudes, and care-seeking behavior toward TB [31]. A short follow-up survey will be conducted at the end of the TB treatment period for each person with TB to collect information on missed doses, side effects, and other TB treatment-related costs incurred.

**Table 2 Tab2:** Endpoints and data collection

Study endpoint	Description	Data source
Primary endpoints		
Case notification rates (cases notified per 10,000 population per year)	Numerator: number of cases notified by the selected districts	Case notification data from CENAT
	Denominator: total population in the OD	Population statistics (Ministry of Planning/Department of Statistics/CENAT)
Additionality (additional number of cases reported compared to historical baseline)	Number of cases notified by the selected districts	Case notification data from CENAT
	Historical data (cases notified in the preceding 3 years)	Historical case notification data from CENAT
Cumulative yield (cases diagnosed per 1000 screened)	Numerator: number of cases reported by each arm	Program data In the control arm, data to be collected from the health centers monthly

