	Denominator: total number of individuals screened	Program data Provincial health department laboratory data to determine the number of people screened at health centers in the control arm
Secondary endpoints		
Treatment outcomes	TB treatment outcomes of all new patients 6 months after treatment initiation	Health centers
Number needed to screen	Numerator: total number of individuals screened	Program data Provincial health department laboratory data to determine the number of people screened at health centers in the control arm
	Denominator: number of cases reported by each arm	Program data Control arm: data to be collected from the health centers monthly
Cost per TB case diagnosed/notified	Direct and indirect medical costs while seeking care for TB Staff and intervention costs Diagnostics and medication costs	Health-care-seeking costs: data to be collected in the baseline and follow-up survey Intervention costs: data to be collected from KHANA, CENAT, and CATA DALYs: data to be extracted from WHO global burden of disease studies and other existing literature
Incremental cost-effectiveness ratio per DALY averted		

*CATA* Cambodia Anti-Tuberculosis Association, *CENAT* National Center for Tuberculosis and Leprosy Control, *DALY* disability-adjusted life year, *OD* operational district, *TB* tuberculosis, *WHO* World Health Organization

Data collectors (project staff from CATA, CENAT, KHANA, and/or health center staff) will be trained to explain the study to the participants, obtain written consent for the surveys (Additional file 2), and administer the questionnaire. The data collectors will brief participants on the nature and purposes of the study and potential risks, and will highlight that information will be kept confidential. Consent for the surveys will be taken by the data collectors in a private space after randomization.

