For the secondary endpoints, we will evaluate the treatment outcome of TB cases detected in this study according to the following categories: treatment completed (without evidence of failure); treatment failed (sputum smear remains positive at month 5 or later of treatment); died (death due to any reasons before and during treatment); lost to follow-up (people newly diagnosed with TB who do not initiate treatment or treatment course that is disrupted for 2 or more successive months); not evaluated (no treatment outcome data available); and cured (sputum smear converted from positive to negative in the final month of the treatment and on at least one earlier assessment at month 2 or month 5) [23]. The number needed to screen to detect one TB case in each arm will be calculated by dividing the total number of persons screened by the number of TB cases detected (i.e., the reciprocal of the absolute cumulative yield). Direct and indirect medical costs that will be incurred before and during health-seeking will be measured based upon the baseline and follow-up questionnaires. Costs for identification of presumptive TB cases and engagement with KAPs for screening, including training and meetings before initiating ACF activities, will be categorized separately from the costs for diagnosis using radiological/bacteriological means and management of people with TB. The incremental cost-effectiveness ratio (ICER) will be estimated by dividing the difference in total costs between trial arms by the difference in the total number of TB cases detected. The ICER per disability-adjusted life year averted will also be considered as a benchmark to determine whether the interventions are cost-effective.

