## Trial status

Protocol version 1, December 3, 2019. Recruitment began on December 18, 2019 and will be completed by approximately December 31, 2020.

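### The 6-month reading of treatment outcome conflicts with end-of-course categories and a 2-month interruption rule, and the calendar leaves no slack to resolve late cases

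*Protocol article*

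**What the plan says.** Treatment outcome is a secondary endpoint. Table 2 defines it as "TB treatment outcomes of all new patients 6 months after treatment initiation", with health centers as the data source. The descriptions of all four arms give the same follow-up; for the control arm it reads "We will follow-up all people with TB diagnosed during the study period for 6 months from the treatment initiation".

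The section on statistical methods for primary and secondary outcomes lists six categories: completed, failed, died, lost to follow-up, not evaluated and cured. Several are results of a whole course. Cure, for example, depends on a smear in the last month of treatment. Loss to follow-up has two routes: "people newly diagnosed with TB who do not initiate treatment", or a "treatment course that is disrupted for 2 or more successive months". The residual category is "not evaluated (no treatment outcome data available").

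On timing, the section on assessment and collection of outcomes says "A short follow-up survey will be conducted at the end of the TB treatment period for each person with TB", and the same section later places that exit interview at the end of the 6-month follow-up. Under Trial status, recruitment began on 18 December 2019 and "will be completed by approximately December 31, 2020". The Abstract says that the trial "will be conducted between December 2019 and June 2021". Table 1 shows individual enrollment ending in Q4 2020 and treatment-outcome collection ending in Q2 2021.

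**The concern.** The document fixes both when the outcome is read and how it is classified, and the two do not fit together. The reading falls at about the planned end of treatment, but one category needs 2 further months to become observable for anyone who stops late, and others need the course to have ended. The reading is also timed from treatment start, while one route to loss to follow-up is never starting.

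At stake is the classification of a secondary endpoint. Late interruptions and overruns have to be placed somewhere, and the article gives no rule for them. If each health center or data collector decides, loss to follow-up will tend to be undercounted and some patients will have no proper outcome. The planned survival analysis of treatment success does not settle this. Success would occur at about the time of the reading, so a small overrun decides whether a patient is counted as a success.

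**Working it through.** **Inputs.** Reading at 6 months from treatment start (Table 2). Interruption rule of 2 months (statistical methods section). Recruitment from 18 December 2019 to about 31 December 2020 (Trial status). Trial end June 2021 (Abstract), taken as 30 June 2021. The course length is not stated; about 6 months is inferred, because the follow-up survey is placed both at the end of treatment and at the end of the 6-month follow-up.

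**1. The plan's own calendar.** 31 December 2020 + 6 months = 30 June 2021. With a same-day treatment start, the last recruited patient reaches the planned reading on the last day of the trial. The stated schedule is reproduced, with zero slack.

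**2. Interruption rule against the reading.** The latest onset that can reach 2 months off treatment by the reading is 6 − 2 = month 4. Onset after month 4 leaves less than 2 months. The affected stretch of a 6-month course is (6 − 4)/6 = 33%. This is a share of treatment time, not of patients.

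Take a patient who stops at month 5, read at month 6:
- lost to follow-up: no, only 1 month off treatment
- completed or cured: no, the course was not finished
- failed or died: no, unless a separate event occurred
- not evaluated: not clearly, since treatment data exist

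A patient still on treatment at month 6 after a short interruption likewise has no final outcome, and there is no category for still being on treatment.

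**3. People who never start.** They are lost to follow-up by definition, but initiation + 6 months has no value without an initiation date. Whether they enter the endpoint, and when, is undefined.

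**4. Slack needed.** An interruption at the very end of a 6-month course becomes scorable at 6 + 2 = month 8. For the last start, 31 December 2020 + 8 months = 31 August 2021. With the end kept at 30 June 2021, a start on 31 October 2020 just reaches month 8, and starts from 1 November do not. The recruitment window is 14 + 366 = 380 days, and November plus December is 61 days.

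| Reading | Assumed delay from diagnosis to treatment | Days not reaching it by 30 June 2021 | Share of 380, even accrual |
|---|---|---|---|
| Month 6 | none | 0 | 0% |
| Month 6 | 7 days | 7 | 1.8% |
| Month 6 | 14 days | 14 | 3.7% |
| Month 6 | 30 days | 30 | 7.9% |
| Month 8 | none | 61 | 16.1% |

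The delays and even accrual are assumptions; the document gives neither.

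**The case against.** The strongest reply is that 6 months is shorthand for the end of treatment. The source is the health-center record, the categories are taken from the national guideline, and collection runs over five quarters. On that reading nothing forces a snapshot at month 6. For the 319 of 380 days of starts (about 84%) that reach month 8 by 30 June 2021, a late interruption could be picked up from the record within the trial. This has force: the document does not rule out a later look, so it would be too strong to say that such losses can never be scored. But it does not plan one either. Table 2 and the arm descriptions all fix 6 months, and even an end-of-course reading leaves the 2-month rule unmet for late interruptions.

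Three stronger readings are tempting and are not supported.

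- **A reader might infer that late-found patients have no outcome because the trial stops in June 2021.** The dates say otherwise: the last same-day start reaches month 6 on 30 June 2021. Only later starts and overruns are exposed.
- **A reader might infer bias between arms, because the one-off screening sessions could bunch treatment starts late.** The session dates are not given, sessions could equally be early, and the 6-month follow-up is common to all four arms.
- **A reader might put a size on the error.** Multiplying an assumed 3–6% on-treatment loss by one third gives 1–2 percentage points. Neither the loss rate nor evenly spread drop-out is in the document. The upper value would use up the whole 6% without success that the 94% national success rate in the Background implies, leaving nothing for death or failure. It would also measure misplacement between categories, not error in treatment success: a late drop-out recorded as not evaluated is still not a success. Success would be overstated only if such patients were taken as completed, which the document nowhere says.

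The article also mentions imputation for missing data. That does not help patients whose status is known but fits no category.

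**Conclusion.** The point holds as a conflict between two rules that the article itself states. At a 6-month reading, interruptions starting after month 4 fit no category, courses that run past 6 months have no final outcome, and people who never start treatment are classified but have no reading date. The calendar meets the 6-month reading exactly and has no room for later starts, overruns or the 2 extra months that late interruptions need; about 16% of patients would not reach month 8 by the trial's end.

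The first two statements assume a course of about 6 months and no use of information after the reading. The 16% assumes even accrual and treatment starting on the day of recruitment. The expected consequence is undercounted loss to follow-up and some unscored patients. How many, and whether arms differ, cannot be derived from the document. The primary endpoints are not touched. It should be corrected, at the weight of a secondary endpoint.

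**What to change.** Reconcile Table 2 with the category definitions:

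- Define the endpoint as the final outcome of the treatment episode in the health-center records, for every diagnosed case eligible for this endpoint, including those who never start treatment.
- Extract it at least 8 months after the last treatment start, which is about the end of August 2021 or later if the last start slips past 31 December 2020.
- Report anyone still on treatment at extraction separately rather than fitting them into an existing category.
- Keep the 6-month survey as planned for costs and missed doses.
- Extend the treatment-outcome row of Table 1 to match.

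The cost is a later extraction from a source already named in the plan and a change of wording. The treatment-outcome results come about one quarter later. Nothing changes in the primary endpoints or in how patients are managed.

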#### Plans to promote participant retention and complete follow-up

The plans to promote participant retention and to manage refusals are illustrated in the previous section “Plans for assessment and collection of outcomes”.

#### Data management

Data coding, quality control, and data entry will be done following established procedures at KHANA and Saw Swee Hock School of Public Health, National University of Singapore. A database will be developed for data entry in KoBoToolbox [32], which includes a built-in range, and within and between-variable consistency checks. The program also runs error-checking applications and produces reports of inconsistencies to be checked daily. The database will be exported into Excel to check for consistency and to clean before data analyses. All data will be entered into the database within 1 month of collection. For baseline data, a precoded questionnaire will be used to minimize data coding errors. All data forms and questionnaires will be checked for errors by the field supervisors, and necessary corrections will be made during data entry.

#### Confidentiality

The steps taken to maintain participants’ confidentiality during the consent-taking process are illustrated in the earlier section “Who will take informed consent?”. Furthermore, only project staff from CATA, CENAT, and KHANA will have access to the personal data in the trial. These data will not be published, and they will be discarded after the publication of results.

#### Plans for collection, laboratory evaluation, and storage of biological specimens for genetic or molecular analysis in this trial/future use

This trial will evaluate four models of case detection to reach people with TB who are undiagnosed effectively. The collection and evaluation of sputum samples and other biological specimens in the course of this trial for the diagnosis and management of TB will be conducted following the standard protocol and guidelines in Cambodia [23]. It is not within the scope of this study to conduct additional analyses on the biological specimens collected. Hence, the management of biological specimens collected in the course of this trial will be under the purview of the NTP as they would normally be handled outside the research.

### Statistical methods

#### Statistical methods for primary and secondary outcomes

For the primary endpoints, we will compute TB case notification at the cluster level by dividing the total number of TB cases (all forms) notified by the selected ODs by the total population in each OD. Case notification rates will be presented as TB cases notified per 100,000 population per year. The difference in the total number of TB cases notified during the intervention period and the number of TB cases notified in the preceding 3 years will be computed to determine additionality. We will calculate the cumulative yield of TB cases by dividing the number of cases notified in each arm by the total number of people screened for TB. Cumulative yield will be presented as TB cases notified per 1000 individuals screened.

For the secondary endpoints, we will evaluate the treatment outcome of TB cases detected in this study according to the following categories: treatment completed (without evidence of failure); treatment failed (sputum smear remains positive at month 5 or later of treatment); died (death due to any reasons before and during treatment); lost to follow-up (people newly diagnosed with TB who do not initiate treatment or treatment course that is disrupted for 2 or more successive months); not evaluated (no treatment outcome data available); and cured (sputum smear converted from positive to negative in the final month of the treatment and on at least one earlier assessment at month 2 or month 5) [23]. The number needed to screen to detect one TB case in each arm will be calculated by dividing the total number of persons screened by the number of TB cases detected (i.e., the reciprocal of the absolute cumulative yield). Direct and indirect medical costs that will be incurred before and during health-seeking will be measured based upon the baseline and follow-up questionnaires. Costs for identification of presumptive TB cases and engagement with KAPs for screening, including training and meetings before initiating ACF activities, will be categorized separately from the costs for diagnosis using radiological/bacteriological means and management of people with TB. The incremental cost-effectiveness ratio (ICER) will be estimated by dividing the difference in total costs between trial arms by the difference in the total number of TB cases detected. The ICER per disability-adjusted life year averted will also be considered as a benchmark to determine whether the interventions are cost-effective.

We will analyze the primary and secondary endpoints by intention to treat, and the analyses will be conducted in two stages. First, we will analyze and present primary and secondary endpoints using the cluster summary method. The baseline characteristics of all arms at the cluster level and individual-level characteristics at baseline and endline will be compared using Student’s *t* test and hierarchical or mixed-effect models to estimate the ratio of these means. As the ODs have several health centers, we will adopt a linear mixed-effects model adjusting for baseline measurements to account for clustering in the data. Individual-level data will also be incorporated into multivariable regression models to account for potential confounders differing by the trial arm and improve the precision of the risk ratios by accounting for intercluster variations. The impact of TB case-finding strategies on treatment outcomes will be evaluated using survival analysis to compare treatment success rates across the intervention and control arms. The study will be reported according to the Consolidated Standards of Reporting Trials (CONSORT) [33] statement (Additional file 3), the template for intervention description and replication (TIDieR) [34] checklist for intervention description and replication (Additional file 4), the Standard Protocol Items: Recommendations for Interventional Trials (SPIRIT) [35] statement (Additional file 5), and the Pragmatic Explanatory Continuum Indicator Summary-2 (PRECIS-2) [36] for pragmatic trials (Additional file 6). All statistical analyses will be conducted using STATA 14 (Stata Corp LP, TX, USA) and R (R Foundation for Statistical Computing, Vienna, Austria).

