### Outcomes

We will measure the following endpoints in all four arms. The primary endpoint will be the case notification rate in the intervention and control ODs during the study period. We define a TB case to be either bacteriologically confirmed (smear-positive identified by smear microscopy, culture, or rapid diagnostics approved by the World Health Organization (WHO)), smear-negative TB (two sputum samples tested negative and clinically diagnosed by a clinician—with abnormal CXR or no improvement in response to a course of broad-spectrum antibiotics), or extrapulmonary TB (presence of local symptoms such as enlarged lymph nodes, joint swelling, and Gibbus deformity and presence of general symptoms such as cough, fever, weight loss, and night sweats) [23]. This will be ascertained from the results of the screening and routine case notification data reported to the NTP. We will also determine: additionality, comparing the yield in each arm with its respective historical baseline (same period in the preceding year); and cumulative yield over the project implementation period. Secondary endpoints will include: the number of people needed to screen to detect one TB case; direct and indirect costs per TB case notified; and the treatment outcome of all people with TB in this study. These data will be collected on the aggregated form at the health center level or as reported by the project implementation team in each arm, except cost data, which will be collected from study participants in the baseline and follow-up surveys.

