#### Frequency and plans for auditing trial conduct

The research team will conduct at least two monitoring visits to each OD during the 1-year implementation period. Field supervisors will also conduct at least four monitoring visits (e.g., every quarter for KHANA arms where the intervention is spread over 1 year and at every screening session conducted by CATA and CENAT during the implementation period, respectively). During monitoring visits, we will review consent forms, completeness of the data collection forms, and compliance with the trial protocol. Any anomalies in recruitment and data will be followed up by the field staff. Interim analyses will be conducted by the data analyst who is otherwise masked to intervention allocation. Data, recruitment processes, and interim results will be monitored by the research team and reported to the DMC.

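### Additionality, listed as a primary endpoint, has two incompatible baselines, and the analysis text read literally subtracts a 3-year count from a count over about 1 to 1.25 years

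*Protocol article*

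**What the plan says.** The abstract states: "The primary endpoints will be TB case notification rates, additionality, and cumulative yield of TB cases". Table 2, in the section on assessment and collection of outcomes, also places additionality under the primary endpoints. The Outcomes section differs: "The primary endpoint will be the case notification rate in the intervention and control ODs during the study period", with additionality mentioned afterwards as a further quantity to be determined.

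The baseline is described three times:

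- **Outcomes:** "additionality, comparing the yield in each arm with its respective historical baseline (same period in the preceding year".
- **Table 2:** the endpoint is "Additionality (additional number of cases reported compared to historical baseline", and the input listed for that baseline is "Historical data (cases notified in the preceding 3 years".
- **Statistical methods for primary and secondary outcomes:** the difference between the total notified "during the intervention period and the number of TB cases notified in the preceding 3 years will be computed to determine additionality".

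On the length of the intervention, the auditing section plans "at least two monitoring visits to each OD during the 1-year implementation period". Trial status gives recruitment from 18 December 2019 to about 31 December 2020. Table 1 marks interventions and notification counts from Q4 2019 to Q4 2020.

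**The concern.** Two things go wrong together. First, one endpoint has two baselines, a single preceding year and three preceding years, and nothing in the article reconciles them. The 3-year wording stands in two separate places, so it is hard to treat as a single slip. Second, the sentence that says how the endpoint is computed subtracts totals over unequal periods. It mentions no mean, no annualising and no matching of calendar periods.

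An analyst who follows that sentence would report a loss of cases where there was a gain. An analyst who corrects it silently must choose a baseline that the article leaves open, possibly after seeing the data. For an endpoint listed as primary, neither is acceptable.

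**Working it through.** The article states no numerical additionality, so there is no figure of its own to reproduce. The check applies the written rule to the article's own durations and planning effects.

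**Inputs**
- N: notified cases per baseline year, assumed constant over the three prior years.
- T: intervention length in years. It is 1.00 from the auditing section. From the Trial status dates it is 380 days / 365.25 = 1.04. From Table 1, if all five marked quarters count in full, it is 1.25.
- e: relative rise in notifications. The Sample size section uses 110%, 98% and 30% in scenario 1, and 75%, 50% and 25% in scenarios 2 to 4.

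**Formulas**
- Statistical methods, read literally: A = T(1 + e)N - 3N.
- Baseline of matching length (the preceding year's same period, or the 3-year mean scaled to T): A = T(1 + e)N - TN = TeN.
- Break-even for the literal rule: e = 3/T - 1.

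**Results, in units of N**

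| Rise e | Literal, T = 1.00 | Literal, T = 1.04 | Literal, T = 1.25 | Matched baseline, T = 1.00 to 1.25 |
|---|---|---|---|---|
| 0 | -2.00 | -1.96 | -1.75 | 0 |
| 25% | -1.75 | -1.70 | -1.44 | 0.25 to 0.31 |
| 30% | -1.70 | -1.65 | -1.38 | 0.30 to 0.38 |
| 98% | -1.02 | -0.94 | -0.53 | 0.98 to 1.23 |
| 100% | -1.00 | -0.92 | -0.50 | 1.00 to 1.25 |
| 110% | -0.90 | -0.82 | -0.38 | 1.10 to 1.38 |

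Break-even is 3/1.00 - 1 = +200%, 3/1.04 - 1 = +188% and 3/1.25 - 1 = +140%. Every planned effect lies below this range.

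**Sensitivity to a trend.** If notifications had been changing by -5% to +5% per year (an assumption), the literal result for a doubling runs from -1.33 to -0.22 across the three values of T, still negative. Here the unit is the yearly count expected in the intervention year without the intervention.

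**If the 3 years were meant as a mean.** Take no effect, T = 1 and a 5% yearly decline, in the same unit:
- The preceding year had 1/0.95 = 1.053, so additionality is 1 - 1.053 = -0.05.
- The 3-year mean is (1.053 + 1.108 + 1.166)/3 = 1.109, so additionality is 1 - 1.109 = -0.11.

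With a 5% yearly rise the two values are +0.05 and +0.09. Averaging removes the gross error but does not make the two definitions agree.

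**The case against.** The best defence is that nobody would carry out the subtraction literally. Table 2 lists the three years as historical data, which is an input and not a formula. The neighbouring sentence on notification rates works per year, and the Outcomes section specifies a matched period. An annualised baseline is therefore plausible as the intent. That much stands, and the negative figures describe the wording, not a result the trial is bound to report. But the averaging is stated nowhere, and the defence leaves the choice between 1 and 3 years open.

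A second defence is that the Outcomes section names only the notification rate as primary. This is correct, and that rate is not affected by the additionality wording. It does not cancel the abstract and Table 2, which list additionality as primary.

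A reader might infer several stronger points that the article does not support:

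- **That additionality credits any secular change to active case finding and leaves no randomised comparison.** The Outcomes section measures the endpoints in all four arms, and the statistical methods plan cluster summaries and a mixed model adjusting for baseline. A between-arm comparison is not excluded; it is only not spelled out for additionality.
- **That a count not scaled to population is an error.** Table 2 defines a count on purpose and places a population rate beside it.
- **That notifications must triple before the literal rule reaches zero.** This holds only for an intervention of exactly 1.00 year.

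In the other direction, counting all 19 months from December 2019 to June 2021 would make a doubling slightly positive (19/12 × 2 - 3 = +0.17N). But the rule refers to the intervention period, and Table 1 ends notification counts in Q4 2020.

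**Conclusion.** The point holds as a contradiction in the baseline of an endpoint listed as primary, together with a computing rule that fails if followed as written. For the intervention lengths the article supports, the literal rule gives a negative value at every planned effect from +25% to +110% and breaks even only at +140% to +200%. These figures assume a flat baseline; a trend of up to 5% per year in either direction does not change the sign for a doubling.

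If an annualised baseline was meant, the remaining discrepancy is smaller, about 0.05N against 0.11N under an assumed 5% yearly decline with no effect, but it is unresolved. It would be wrong to conclude that the trial's main comparison of notification rates is compromised. This is also not detail that can simply be left to an analysis plan, because the article states two rules that cannot both be followed.

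**What to change.** State one baseline in the same words in Outcomes, Table 2 and the statistical methods, matched in length to the intervention period. Either of these serves:

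- the same period in the preceding year; or
- the mean of the three preceding years, scaled to the intervention length.

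Give the start and end dates of the intervention window. If it exceeds 12 months, the same period one year earlier overlaps it: by 14 days for 18 December 2019 to 31 December 2020, and by a full quarter for Q4 2019 to Q4 2020. The wording should say how this is handled.

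State once whether additionality is primary, so that the abstract, Table 2 and Outcomes agree.

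Because additionality is computed in all four arms, add a sentence that each active case-finding arm's value will be reported beside, and relative to, that of the passive case-finding arm, so that secular change is not read as an effect. The endpoint can stay a count; a new rate-based estimand is not needed to repair this defect.

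The cost is wording. The 3-year history is already a listed data source. The scaled mean needs only annual totals, while a matched calendar period needs monthly or quarterly counts, and Table 2 does not state the resolution of the history. The choice should be recorded before outcome data are analysed.
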